#### Radiological Examination

Ultrasonography of the abdomen will be performed to evaluate the polycystic ovary morphology and grading of fatty liver (NAFLD) and nonalcoholic pancreatic steatosis. The US will be performed at all centers, and MRI of the pelvis (n=100) will be performed primarily at SKIMS, Srinagar, to compare US and standardization of US technique by 2 independent radiologists. MRI will be done as per a randomized selection proportional to the subjects at the site.

#### Laboratory Evaluation

The OGTT will be performed after an overnight fast of 10-12 hours. An oral glucose load with 75 g of anhydrous glucose dissolved in 250-350 mL of water will be administered over 3-5 minutes immediately after the basal sample. The blood samples for LH, FSH, testosterone, AMH, SHBG, and DHEAS will be collected on days 3-7 (early follicular phase) of spontaneous or medroxyprogesterone-induced (in amenorrhea patients) menstrual cycle to confirm PCOS. Hematological parameters (hemoglobin, red blood cells, white blood cells, etc), biochemical tests like lipid profile, liver function, kidney function, blood glucose (OGTT), and hormonal assays like T_4_, thyrotropin, LH, FSH, PRL, E2, P4, cortisol, testosterone, AMH, DHEAS, 17OHP, and insulin at 0 hours, 30 minutes, and 2 hours (optional) will be carried out at the respective centers, and special hormones like testosterone and SHBG will be done in the central facility to be created at the coordinating center (SKIMS, Srinagar). On the day of testing, women will be called after 10-12 hours of fast, and blood samples (15 ml) will be drawn. Blood will be also collected for glucose and insulin estimation after 30 minutes and 120 minutes of 75 g oral glucose challenge. Insulin samples will be immediately put in a refrigerator, separated in cold centrifuge, and stored at −20 °C until the assay. Plasma will be separated in a refrigerated centrifuge at 1560*g* for 10 minutes, and sera will be stored at −80 °C until tested.

Plasma glucose will be measured using the glucose oxidase–peroxidase method, and hormonal tests (LH, FSH, T_4_, thyrotropin, PRL, E2, cortisol, testosterone, AMH, hsCRP, cytokines, and 25OHD) will use ECLIA on Cobas e411 (Roche Diagnostics USA).

### Methodology: Protocol for Substudy 3

The study will be conducted only at 2 centers: AIIMS, New Delhi, and SKIMS, Srinagar. Women (aged 18-40 years) residing in the communities (rural and urban) identified in the prevalence study and those attending outpatient clinics in the departments of either endocrinology, gynecology, or dermatology of the selected institutes who are willing to participate will be recruited in the interventional part of the study. All these women will undergo clinical, biochemical, and hormonal assessment at baseline and at 3 and 6 months (Figure 4).

**Figure 4 figure4:**
[figure not shown]
Study design and workflow chart of substudy 3. 17-OHP: 17-hydroxyprogesterone; AMH: anti-Müllerian hormone; BP: blood pressure; DHEA-S: dehydroepiandrosterone sulfate; FG: Ferriman-Gallwey; FSH: follicle-stimulating hormone; LH: luteinizing hormone; OCP: oral contraceptive pill; OGTT: oral glucose tolerance test; PCOS: polycystic ovary syndrome; PRL: prolactin; SHBG: sex hormone–binding globulin; T4: thyroxine; TSH: thyrotropin.

#### Sample Size Calculation for Substudy 3

On the basis of one study, metformin could improve the Homeostatic Model Assessment of IR from 2.5 (SD 0.39) to 2.79 (SD 0.39) [38]. Assuming that the baseline was similar, at an α error of 0.05 with power of 90%, and with a projected attrition rate of 20%, we need to recruit 153 women per group. To round off, we will recruit and randomize 160 women with PCOS per group (ie, a total of 320 women). A total of 160 subjects will be recruited and randomized in each of the 2 groups, with 80 subjects in each arm.

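### Substudy 3: the 153 women per group do not follow from the printed inputs on either reading of group, and the planning change called an improvement is a rise in insulin resistance

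*Protocol article*

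**What the plan says.** The section Sample Size Calculation for Substudy 3 rests on one cited study, from which it takes that "metformin could improve the Homeostatic Model Assessment of IR from 2.5 (SD 0.39) to 2.79 (SD 0.39"). It assumes similar baselines and works "at an α error of 0.05 with power of 90"%. Then, "with a projected attrition rate of 20%, we need to recruit 153 women per group". The number is rounded up: "we will recruit and randomize 160 women with PCOS per group (ie, a total of 320 women"). The next sentence describes the women as "randomized in each of the 2 groups, with 80 subjects in each arm".

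Other sections bear on what a group is:

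- The Plain English Summary describes the trial as oral contraceptive pills versus metformin.
- Randomization (Drug Intervention) defines Arm A as metformin plus lifestyle versus lifestyle alone, and Arm B as the contraceptive plus lifestyle versus lifestyle alone. Each has 160 women, 80 per center.
- Subject Selection divides the 320 women into 80 for each arm at each center.

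Statistical Analysis names the Student t test and analysis of variance for comparing groups.

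**The concern.** The calculation prints every input that a two-sample comparison of means needs, and also prints the result, so the two can be checked against each other. They disagree. The printed effect is large, about three quarters of an SD, yet the stated number is one that would suit a clearly smaller effect.

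The planning sentence also contradicts itself. The protocol's own abbreviation list expands IR as insulin resistance, so a move from 2.5 to 2.79 is a rise in insulin resistance, yet it is called an improvement.

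This is the only sizing statement for the randomized part of the study, which serves the third primary objective. As printed, a reader cannot tell what effect the trial was sized to detect or what power it has.

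**Working it through.** **Inputs** (all from Sample Size Calculation for Substudy 3): means 2.5 and 2.79, so an absolute difference of 0.29; SD 0.39 at both points; alpha 0.05; power 90%; attrition 20%. Sidedness is not stated for substudy 3, so two-sided is assumed and one-sided is also tried.

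**Step 1: try to reproduce 153.**

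Standardized difference: d = 0.29 / 0.39 = 0.744.

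Normal approximation per treatment: n = 2(1.960 + 1.282)² / 0.744² = 38.0. The t test gives 39.0.

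Attrition: 39 / 0.8 = 48.75, so 49 recruited per treatment. (Multiplying by 1.2 instead gives 47.)

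Two-arm comparison: 2 × 39 / 0.8 = 97.5, so 98 recruited.

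The stated 153 is about 3.1 times 49 (153 / 49) if a group is one treatment, and about 1.6 times 98 (153 / 98) if it is a two-arm comparison.

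**Step 2: look for a variant that gives 153.**

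| Variant | Recruited per treatment | Recruited per two-arm comparison |
|---|---|---|
| Two-sided, 90% power (as printed) | 49 | 98 |
| One-sided, 90% power | 39 | 78 |
| Two-sided, 80% power | 37 | 73 |
| Two-sided, 95% power | 60 | 120 |
| Alpha halved to 0.025 | 57 | 113 |

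A paired design or an allowance for a rank test does not reach 153 either.

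**Step 3: power of 153 per group at the printed effect (d = 0.744).**

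- Group is a two-arm comparison: 153 / 2 = 76.5 per arm; × 0.8 = about 61 evaluable per arm; power about 98.3%.
- Group is one treatment: 153 × 0.8 = about 122 evaluable; power 99.99%.

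Neither is 90%.

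**Step 4: what 153 would imply at 90% power.**

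- Group is one treatment (122 evaluable): d is about 0.417, that is, a difference of about 0.16 at SD 0.39, or an SD of about 0.70 at a difference of 0.29.
- Group is a two-arm comparison (61 per arm): d is about 0.59, that is, a difference of about 0.23 at SD 0.39, or an SD of about 0.49 at a difference of 0.29.

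None of these values is printed.

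**Step 5: power of the planned 320 at the printed effect.** With 80 per treatment, 80 × 0.8 = 64 are evaluable and power is about 98.7%. With 160 per treatment, 128 are evaluable and power is above 99.9%.

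**Step 6: direction.** A two-sided calculation uses only the absolute difference. Swapping 2.5 and 2.79 repairs the wording but leaves 0.29, and therefore 49 per treatment.

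**The case against.** The best defense is that an input was left out, not that the arithmetic failed. The planning sentence describes a change over time, so the calculation may have used the SD of a change score, 0.39 × √(2(1 − r)). With r = 0.2 this is 0.39 × √1.6 = 0.493. Then d = 0.29 / 0.493 = 0.588, the t test needs about 62 evaluable per arm, and 61.8 / 0.8 × 2 gives about 154 per two-arm comparison. That is close to 153, and a condensed article might omit the correlation. It remains a conjecture: no correlation or change-score SD is printed, and the text presents its number as following from the inputs it gives. It does mean that 49 per treatment is right only if the printed inputs are the complete inputs.

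A second objection is that a group is a two-arm comparison, because the women are later described as "randomized in each of the 2 groups, with 80 subjects in each arm". This has force. The excess is then about 1.6-fold, so the 3.1-fold figure must stay conditional. It does not rescue 153.

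Two stronger readings are tempting and are not supported. A reader might infer that the trial has only about 65% power. That figure takes d = 0.417 from 153 read as one treatment and then applies it to 64 evaluable women per treatment, so it needs the meaning of group to change between sentences. Read consistently, the planned numbers reach about 90% at the effect that 153 implies: about 91% with 64 per arm at d = 0.59, and about 91% with 128 per treatment at d = 0.417. A reader might also infer that the reversed direction makes the power figure wrong, or that the plan hypothesizes harm from metformin. Direction does not enter a two-sided calculation, and the sentence plainly intends a benefit; swapped values would be enough to explain it.

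**Conclusion.** The point holds in this form. The stated 153 per group and 90% power do not follow from the printed inputs on either reading of group: the inputs need 49 recruited per treatment or 98 per two-arm comparison, and 153 would give about 98% or above 99.9% power. Separately, the planning change is described in the wrong direction, which shows that a printed mean or the order of the means is wrong but does not by itself alter the number.

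The figures assume a two-sided two-sample t test, 20% attrition applied by dividing by 0.8, and no inputs beyond those printed. A one-sided test would move the requirement further below 153. No loss of power is demonstrated: at the printed effect the planned 320 exceeds 90% whichever way a group is read. What is wrong is the stated basis for the size of the randomized trial. Because the planning effect is itself in doubt, its real power cannot be read from the document.

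**What to change.** 1. Check both means and both SDs against the cited study, and correct the values or their order so that the stated improvement is a fall in the index.
2. Say whether a group is one treatment or a two-arm comparison, and reconcile the Plain English Summary, Sample Size Calculation for Substudy 3, Randomization (Drug Intervention) and Subject Selection on this.
3. State the sidedness of alpha, and print any further input used, such as a change-score SD or a correlation.
4. Restate the required number and the power of the planned 320. If the printed inputs stand and are complete, state 39 evaluable and 49 recruited per treatment, with about 99% power at 80 per treatment (64 evaluable). If another effect or SD was meant, print it and give the power at the planned number per treatment. The 65% figure would apply only if 153 was meant per treatment while 80 per treatment are enrolled.

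Recruitment stays at 320. The cost is a check of one source, one recalculation and a few sentences; no women are added.

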## Plain English Summary

Polycystic ovary syndrome (PCOS) is a multifactorial disorder with unknown etiology and numerous clinical manifestations in reproductive-aged women around the world. The metabolic abnormalities linked to this syndrome include type 2 diabetes, insulin resistance (IR) obesity, abnormal glucose tolerance (AGT), and cardiovascular diseases (CVD). The sketchy data and escalating prevalence of PCOS and associated comorbidities among Indian women led to organization of a multidisciplinary brainstorming meeting held September 11, 2014, at Indian Council of Medical Research (ICMR) headquarters, and the ensuing recommendations suggested formulation of the ICMR–PCOS Task Force to conduct a multicentric, multiphase study among Indian women with PCOS.

This is a multicentric, multispecialty study with a common comprehensive predesigned protocol involving 10 centers located in the 6 zones of the country. The women from the community (rural and urban) will be screened using a validated screening questionnaire, after obtaining a written informed consent from the subjects. The proforma will capture all details about menstrual cyclicity, acne, hirsutism, socioeconomic status, family history of PCOS, etc. The national prevalence will be calculated from the community pool for substudy 1. All biochemical and hormonal analysis will be done by standard assays using similar kits, reagents, and equipment. Ultrasonography (US) including magnetic resonance imaging (MRI) of the abdomen will be performed using a common approved protocol. The various comorbidities such as AGT, nonalcoholic steatohepatitis, and sleep apnea will be evaluated from both the pools (ie, hospital cohort and community cohort in substudy 2). The interventional randomized double-blind trial (ie, oral contraceptive pills [OCPs] vs metformin) will be conducted at only 2 centers for substudy 3. Apart from this, a knowledge, attitude, and practices survey of service providers in the public health system will be conducted to understand the training needs and gaps in the health system addressing PCOS management.

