#### Primary Objectives

The primary objectives are to (1) estimate national prevalence, phenotypic variations, and risk factors of PCOS in the community; (2) estimate the burden of comorbidities such as metabolic syndrome, dyslipidemia, cardiovascular complications, NAFLD, psychiatric abnormalities, sleep apnea, AGT including type 2 diabetes, and impairment of quality of life (QOL) among known cases of PCOS; and (3) compare the variation in efficacy of standard therapeutic modalities for metabolic dysfunction in women with PCOS (2 sites, All India Institute of Medical Sciences [AIIMS] and Sher-i-Kashmir Institute of Medical Sciences [SKIMS]).

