#### Randomization (Drug Intervention)

Eligible consenting subjects will be randomized in a 1:1 ratio into 2 arms through a blinding procedure.

Arm A compares lifestyle (32 kcal/kg diet per day with 55% carbohydrates, 20% protein, 20% fat, and 20 g of fiber with 30 minutes of brisk walking daily) and metformin (1 g /day) versus lifestyle alone (n=160; 80 per center).

Arm B compares lifestyle (32 kcal/kg diet/day with 55% carbohydrates, 20% protein, 20% fat, and 20 g of fiber with 30 minutes of brisk walking daily) and OCP (30 µg ethinyl estradiol plus 2 mg drospirenone) versus lifestyle alone (n=160; 80 per center).

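### Substudy 3 is sized on a rise in HOMA-IR described as an improvement, and reversing the direction still does not give the stated 153 women per group

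*Protocol article*

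**What the plan says.** The section on the sample size for substudy 3 takes its planning effect from one cited study, in which "metformin could improve the Homeostatic Model Assessment of IR from 2.5 (SD 0.39) to 2.79 (SD 0.39"). It then adds the remaining inputs: "Assuming that the baseline was similar", "at an α error of 0.05 with power of 90"%, and "with a projected attrition rate of 20"%. From these it concludes that "we need to recruit 153 women per group", which it rounds up to 160 per group and 320 in total.

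The section on randomization for the drug intervention says "Eligible consenting subjects will be randomized in a 1:1 ratio into 2 arms". It describes each arm as a drug plus lifestyle compared with lifestyle alone, with 160 women per arm and 80 per center.

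The article uses IR for insulin resistance and treats it as harmful. The Plain English Summary says: "The metabolic abnormalities linked to this syndrome include type 2 diabetes, insulin resistance (IR) obesity".

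**The concern.** A higher value on an insulin-resistance index means more resistance. The sentence describes a move from 2.5 up to 2.79 and calls it an improvement, so the verb and the numbers disagree. Nothing else in the article resolves this: it does not mention an inverse scale, say which value belongs to which group, or report a correction.

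This is the only treatment effect given for substudy 3, and 153, 160 and 320 all rest on it. A reader cannot tell what benefit the trial is meant to detect, from what starting value, or whether the contrast is a change within women or a difference between groups. The natural repair is to swap the two means and leave the rest. That repair is sufficient only if the stated sample size follows from the stated magnitudes, so this has to be checked.

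**Working it through.** **Inputs.** All come from the section on the sample size for substudy 3, except the allocation ratio, which comes from the section on randomization.
- Means 2.5 and 2.79; SD 0.39 for both
- Alpha 0.05 (sidedness not stated; two-sided taken as the main case)
- Power 90%
- Attrition 20%
- Allocation 1:1
- Stated result: 153 recruited per group

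**Direction.** 2.79 − 2.50 = +0.29. As printed, this is a rise of 0.29/2.50 = 11.6%. With the means swapped, it is a fall of 0.29/2.79 = 10.4%.

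**Attempt to reproduce 153.** For two means with equal groups,

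n per group = 2 (z₁₋α/₂ + z₁₋β)² (SD/δ)²

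- (1.960 + 1.282)² = 10.507
- (0.39/0.29)² = 1.8086
- n = 2 × 10.507 × 1.8086 = 38.01, rounded up to 39 evaluable per group (the t-based calculation also gives 39)
- Allowing for attrition: 39/(1 − 0.20) = 48.75, so 49 recruited per group

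Because δ enters as a square, δ = −0.29 gives the same 39 and 49.

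**Other readings of the same inputs.**

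| Reading | Evaluable per group | Recruited per group (n/0.8) |
|---|---|---|
| Two-sided, SD 0.39 | 39 | 49 |
| One-sided, SD 0.39 | 31 | 39 |
| Two-sided, alpha 0.025 (two comparisons) | 45 | 57 |
| Two-sided, SD × √2 = 0.552 (change score) | 77 | 97 |

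None gives 153. Multiplying by 1.2 instead of dividing by 0.8 gives 47 in the main case.

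**What 153 would require.** 153 × 0.8 = 122.4 evaluable per group. With SD 0.39 that corresponds to δ = 0.39 × √(2/122.4) × 3.242 ≈ 0.162. With δ = 0.29 it corresponds to an SD of about 0.70. Halving δ to 0.145, or doubling the SD to 0.78, gives exactly 153 per group, but before any attrition allowance; with it the number is 192.

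**Power at the planned size, if the magnitudes are right.** Taking 0.29 as a between-group difference with SD 0.39, power ≈ Φ(0.7436 × √(n/2) − 1.960).
- n = 64 (80 less 20%): Φ(4.206 − 1.960) = 98.8%; the t-based value is 98.7%
- n = 128 (160 less 20%): Φ(5.949 − 1.960), above 99.9%

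Both group sizes are shown because the article refers to 160 women per group or arm and also to 80 per arm or center.

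**The case against.** The strongest reply is that this is a slip of wording. The word for benefit shows what was intended, the index is named, and a two-sided calculation depends only on the size of the difference. On this view, swapping the means changes nothing. The article's remark that baselines were assumed similar also allows a harmless reading: 2.5 under metformin against 2.79 under the comparator at follow-up, badly phrased as a change.

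Part of this stands. The sign has no effect on a two-sided sample size, and the between-group reading is as plausible as a transposition. What does not stand is the inference that the stated size is sound once the direction is corrected. The same magnitudes give 49 recruited per group and not 153, whichever way they run. Either the printed effect is not the one used, or some other input or step is missing.

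A reader might go further and infer that the source used a different index, that it showed no benefit, or that the trial was planned to detect harm. The article supports none of these. It names HOMA-IR and intends a benefit, and only the cited study, which is not available here, could settle what it found.

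**Conclusion.** The planning effect for substudy 3 is wrong as written: a rise of 0.29 in an insulin-resistance index is presented as an improvement. The article cannot show whether the means are transposed, a between-group contrast is worded as a change, or the values are misreported.

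The numerical consequence lies in the magnitudes and not in the sign. The stated inputs give about 39 evaluable and 49 recruited women per group, roughly a third of the stated 153. This assumes a two-sided comparison of two means with equal groups and division by 0.8 for attrition. The one-sided, split-alpha and change-score variants do not reach 153 either.

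A reader might conclude that the trial is underpowered. The documents do not support that. If 0.29 and 0.39 are correct as a between-group difference and its SD, power at the planned size is about 98.7% or more. If they are not, the power cannot be computed from the article. This should be corrected, because the stated justification for the size of a randomized comparison cannot be interpreted at present, but it is not evidence that 320 women are too few.

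**What to change.** 1. Check the cited study and correct the sentence. State the target as a reduction in HOMA-IR and say which value is the baseline or comparator, whether the contrast is within-group or between-group, and which SD belongs to that contrast.
2. State whether alpha is one- or two-sided and how many women enter each comparison after attrition.
3. Restate the power for the 320 women already planned, using the corrected difference and SD, and either show how 153 was obtained or withdraw it. Swapping the two means without this step leaves the discrepancy in place.

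The cost is one reference check, one short recalculation and a rewritten paragraph. Trial conduct does not change. The restated power may be higher or lower than the stated 90%, depending on what the source reports.

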#### Randomization (Drug Intervention)

Eligible consenting subjects will be randomized in a 1:1 ratio into 2 arms through a blinding procedure.

Arm A compares lifestyle (32 kcal/kg diet per day with 55% carbohydrates, 20% protein, 20% fat, and 20 g of fiber with 30 minutes of brisk walking daily) and metformin (1 g /day) versus lifestyle alone (n=160; 80 per center).

Arm B compares lifestyle (32 kcal/kg diet/day with 55% carbohydrates, 20% protein, 20% fat, and 20 g of fiber with 30 minutes of brisk walking daily) and OCP (30 µg ethinyl estradiol plus 2 mg drospirenone) versus lifestyle alone (n=160; 80 per center).

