The drug-naïve women who qualify on the 1990 NIH criteria (from both the institutional pool and the community pool) will be invited for the study. This will be an open-label randomized intervention trial and will follow a common protocol at each participating center. Women who do not desire fertility and who furnish written informed consent (second time) will undergo a detailed clinical assessment including details of menstrual, drug, and other relevant history followed by clinical examination involving anthropometry (height, weight, waist circumference); Ferriman-Gallwey scoring for hirsutism; grading of acanthosis nigricans, androgenic alopecia, and acne vulgaris (grades 1-3); blood pressure measurement; and a brief relevant systemic examination. Biochemical and hormone estimation will be done at baseline from the second day to the seventh day of the menstruation cycle and at 3 and 6 months. The subjects will be followed up at 6 months, and all these investigations will be repeated at the follow-up. A total of 320 women for the intervention phase (ie, 80 subjects per arm and per center) will be recruited. The study will be done only in 2 participating centers (SKIMS, Srinagar, and AIIMS, New Delhi). The intervention phase will be initially done for a period of 24 weeks.

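### Substudy 3 is given incompatible descriptions of its blinding, its randomised contrast and its number of women per treatment, so what it tests and at what size is undefined

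*Protocol article*

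**What the plan says.** Five places in the protocol article describe the design of substudy 3.

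- **Abstract, Methods:** 1:1 randomisation into 2 arms by a blinding procedure.
- **Plain English Summary:** "The interventional randomized double-blind trial (ie, oral contraceptive pills [OCPs] vs metformin) will be conducted at only 2 centers for substudy 3".
- **Sample Size Calculation for Substudy 3:** 153 women per group are needed, rounded to 160 per group and 320 in total. The section then adds "A total of 160 subjects will be recruited and randomized in each of the 2 groups, with 80 subjects in each arm" as its closing sentence.
- **Randomization (Drug Intervention):** the section opens with this rule: "Eligible consenting subjects will be randomized in a 1:1 ratio into 2 arms through a blinding procedure". It then defines the two arms. Arm A is lifestyle "and metformin (1 g /day) versus lifestyle alone (n=160; 80 per center"). Arm B is lifestyle "and OCP (30 µg ethinyl estradiol plus 2 mg drospirenone) versus lifestyle alone (n=160; 80 per center").
- **Subject Selection (substudy 3):** "This will be an open-label randomized intervention trial and will follow a common protocol at each participating center". The same section gives 320 women in all, as 80 for each arm and each center.

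The sizing rests on one effect: "metformin could improve the Homeostatic Model Assessment of IR from 2.5 (SD 0.39) to 2.79 (SD 0.39"), with alpha 0.05, power 90% and attrition 20%.

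**The concern.** Three features that define a randomised trial are each described in more than one way.

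**Blinding.** Double-blind and open-label exclude each other. A blinding procedure is also not a method of randomisation; the phrase may have been meant to describe concealed allocation. As described, drug plus lifestyle against lifestyle alone has no placebo, so that contrast could not be double-blind. This matters most for the signs graded by an observer in substudy 3: Ferriman-Gallwey score, acne, androgenic alopecia and acanthosis nigricans. A double-blind label would understate their risk of bias.

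**Contrast.** The trial could compare metformin with the contraceptive, or each drug with lifestyle alone. A 1:1 split between Arm A and Arm B does not by itself create a randomised lifestyle-alone group, and the Randomization section states no second allocation within an arm. A reader cannot tell whether there are two, three or four randomised groups. Primary objective 3, which speaks of comparing the efficacy of standard treatments, does not settle it.

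**Size.** The number of women per randomised treatment depends on which section is followed.

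Left open, the primary contrast and the risk-of-bias label could be chosen after the data are seen.

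**Working it through.** **1. The three uses of 80.**

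| Section | What 160 refers to | What 80 refers to |
|---|---|---|
| Sample Size Calculation | one group | one arm within a group |
| Randomization | one whole comparison (drug and lifestyle-alone together) | one center within a comparison |
| Subject Selection | not stated | one arm at one center |

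*Reading 1:* each comparison of 160 is split 1:1, giving 80 per treatment. Total 4 × 80 = 320.

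*Reading 2:* two arms, each with 80 at each of two centers, giving 160 per arm. Total 2 × 2 × 80 = 320.

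The total is the same, so it cannot show which reading is meant. Reading 1 gives 80/153 = 52% of the stated requirement. Reading 2 meets it.

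**2. The plan's own figure.** Inputs: difference 2.79 − 2.5 = 0.29; SD 0.39; two-sided alpha 0.05 (sidedness is not stated, so this is an assumption); power 90%. Only the size of the difference is used here.

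n per group = 2 × (1.960 + 1.282)² × (0.39/0.29)² = 38.01, so 39.

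With 20% attrition: 39/0.8 = 48.75, so 49. A one-sided test gives 31, then 39. The stated 153 is not reproduced. It appears only if the SD is doubled to 0.78 with no attrition allowance (152.03, so 153; with attrition 153/0.8 = 191.25, so 192), which is not what the text says.

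**3. Power under each reading.** Evaluable women: 80 × 0.8 = 64, or 160 × 0.8 = 128, per treatment. Power = Φ(d√(n/2) − 1.960).

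- *At the stated inputs*, d = 0.29/0.39 = 0.744. With 64 per treatment: 0.744 × √32 = 4.21, power 98.8%. With 128, power exceeds 99.9%.
- *At the effect that would make 153 correct:* 153 × 0.8 = 122.4 evaluable, so d = √2 × 3.242/√122.4 = 0.414. With 64 per treatment, power is 65%; with 128, 91%.

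The second line shows only how much the two readings differ if 153 is taken at face value. The document does not state an effect of 0.414.

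**4. Which contrast was sized.** The only effect quoted is for metformin. None is given for the contraceptive against lifestyle, or for metformin against the contraceptive, so the sizing does not identify the primary contrast.

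**5. If two lifestyle-alone groups exist.** The SE factor for one drug against its own control is √(1/64 + 1/64) = 0.177. Against both controls treated as one group it is √(1/64 + 1/128) = 0.153, which is 13% smaller. That gain requires the two control groups to be exchangeable. If each drug sits on its own randomisation list and the model carries a freely estimated list effect, four cells are fitted with four parameters and the SE returns to 0.177.

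**The case against.** The strongest reply is that a coherent trial can be read out of the text: 1:1 into two arms, metformin against the contraceptive, 80 women per arm at each of two centers. That is 160 against 160 and agrees with 153 rounded up. This reading is available, and for that reason 80 per treatment cannot be presented as fact. It does not clear the text, because it ignores the lifestyle-alone comparators in the Randomization section and the 80 per arm in the sample size section. That last sentence can also be taken to mean randomisation within each group, which would create lifestyle-alone controls.

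A second reply is that an article is condensed and Figure 4 is not shown, so a placebo could exist in the full protocol. That limits what can be made of the missing placebo. It does not reconcile double-blind with open-label, both of which are printed.

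A third is that the sizing outcome, HOMA-IR, is a laboratory measure and less exposed to unblinded assessment. That is correct, and it confines the bias concern mainly to the observer-graded signs. Quality of life should not be added to them, because it is not among the listed substudy 3 assessments.

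A reader might infer that the drug-against-lifestyle comparisons are underpowered, at 65%. The document does not support this: the figure depends on Reading 1 and on an effect solved backwards from a 153 that its own inputs do not give.

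**Conclusion.** The inconsistency stands and needs correction before any substudy 3 result is interpreted. Blinding, the randomised contrast and the n per treatment are each stated in ways that cannot all hold. The n per treatment differs by a factor of two between readings (80 or 160).

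Low power is not shown. At the stated 0.29 and 0.39, and assuming a two-sided test and 20% attrition, even the smaller reading gives about 99% power. That 153 does not follow from those inputs is a separate sample-size error; it also means that 153 is not a sound yardstick for a shortfall.

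Nor does the text show that the trial ought to be a three-group design with one shared lifestyle-alone group. Keeping two control groups apart is a choice about precision, not an error. If metformin against the contraceptive is the intended contrast, such a layout would leave 80 rather than 160 women on each drug.

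**What to change.** Reconcile the abstract Methods, the Plain English Summary, and the substudy 3 sections on sample size, randomization and subject selection. The Results section reports that the intervention began in 2018, so the text should be brought into line with the allocation actually used, not with a new layout. State:

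1. the randomised groups and the list or lists they were drawn from;
2. the primary contrast;
3. the n and power for each contrast, by treatment and by center, with the sample-size inputs corrected so that they give the number quoted.

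Replace the double-blind label and the blinding-procedure phrase with open-label with concealed allocation, unless a blinded comparison was actually run; if one was, say who was blinded and how. Report the observer-graded signs with that status made plain.

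If two separately randomised lifestyle-alone groups exist, the sponsor may pool them. This is optional. A term for the randomisation list guards against differences between the lists, but the 13% smaller SE is obtained only where the groups are treated as exchangeable and no free list effect is fitted. Any pooling should be justified on that basis and fixed before the outcomes are compared.

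The cost is wording and a restated power calculation, with no extra women or procedures. If the records show that no lifestyle-alone group was randomised, the claims against lifestyle alone would have to be withdrawn.
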